We will do sensitivity analysis for the primary outcome using methods which do not assume a MAR mechanism such as pattern-mixture models, to assess the robustness of this assumption. If different results are obtained from a pattern-mixture model compared to the mixed effects model then it is likely that the MAR assumption is not valid. As part of our exploration of treatment effects we will also produce a per-protocol or completer analysis with appropriate caveats.

*Sample size*

Although, previous studies and the recent systematic review have suggested a large treatment effect observed with supported internet-delivered interventions, we believe this treatment effect is too optimistic for a self-guided treatment, especially in a sub-clinical population group, and is also likely to be smaller in pragmatic settings. For this reason, we intend to recruit 2104 participants (i.e. 1052 per group) to this trial, which will provide 90% power to detect a small between group effect size of Cohen's d=0.2 at 5% two-sided significant level. A small effect like this may not be that important to the individual but is potentially important in population terms, in a public health intervention. This sample size has also accounted for a high level of potential attrition of up to 50% (obviously we will aim to mitigate this through frequent email and text message reminders but we need to be realistic about self-guided internet interventions and the likely level of attrition). We believe this is entirely feasible and achievable using our previous recruitment strategy and given the high population prevalence of social anxiety symptoms.

*Economic evaluation*

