A prospective economic evaluation, conducted from a NHS and social care perspective, will be integrated into the trial to assess cost and cost-effectiveness of the self-guided internet-based intervention for people with pre-clinical social anxiety symptoms. Primary research methods will be followed to estimate the costs of delivering the intervention, including development and maintenance costs for the website, advertisement costs, and the costs of monitoring participants for safety or other reasons. Taking a NHS and social care perspective means that broader health service and social care utilization costs will be included in the primary economic evaluation. Health service and social care utilisation data will be collected through participant self-report questionnaires administered at baseline, and each follow-up time point. Unit costs for service utilisation will be derived from standard national sources such as Unit Costs of Health and Social Care (PSSRU), NHS reference cost etc. ,and estimated in line with best practice. Costs will be standardised to current prices where possible. Given the fact that the intervention will target people who are unlikely to pursue help from NHS or social care due to the sub-clinical mild nature of the symptoms, we don’t expect the intervention to have significant impact on health and social care costs. On the other hand, these symptoms may impact on people’s social life which leads to loss of productivities due to leaves from work, study, or absent from leisure activities. We will collect data to assess this wider social impact.

The effectiveness of the intervention will be measured using Quality-Adjusted Life Years (QALYs) using the under the curve approach. Quality of life will be measured at baseline, 6 weeks, 3 months, 6 months, and 12 months using the SF-36. The data will be converted into SF-6D health utilities using established UK based utility algorithms and combined with time duration data (e.g. 6 weeks, 3 months, and 6 months according to the follow up time points from baseline) calculate quality-adjusted life years (QALYs). We are using the SF-6D (derived from SF36), which is a widely accepted generic preference-based measure because we have problems to integrate an online version of the EQ5D and portal to our trial design

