The results of the economic evaluation will primarily be expressed in terms of incremental cost per QALY gained between the intervention and control groups. Missing data for both costs and SF-36 will be explored using the same strategies of the statistical analysis. Multiple imputation approach will be used to handle missing data. Non-parametric bootstrap estimation will be used to calculate 95% confidence intervals for mean difference of cost and QALYs between the trial groups, and incremental cost effectiveness ratios. Regression will be used to obtain incremental cost-effectiveness ratios after controlling for baseline respondent’s characteristics. A series of sensitivity analyses will explore the implications of uncertainty on the incremental cost-effectiveness ratios and will consider the broader issue of the generalisability of the results. Cost-effectiveness acceptability curves will be constructed using the net benefits approach.

*Qualitative study*

We will collect qualitative survey data (free text box) on initial views and experiences of the intervention for all participants in the intervention arm at six weeks. These data will be analysed using content analysis and where appropriate thematic analysis. In addition, a qualitative interview study will be conducted with a subset of approximately 20 participants in the intervention arm at 12 months and with those who withdraw from the trial. The latter interviews will focus on reasons for withdrawal. For those who complete the trial, a maximum-variation sampling technique will be used to select a diverse sample of potential interviewees based on demographic information and degree of completion of the intervention. Interviews will be audiorecorded, they will last approximately one hour and will be conducted in the participant’s home or (if inconvenient or impractical to conduct a home visit) by telephone. They will follow a semi-structured topic guide that will be piloted. Interview transcripts will be analysed iteratively and thematically using a constant comparative approach, to explore issues related to acceptability, usability, adherence, attrition, and perceived value and impact of the intervention. This investigation will be led by the internationally leading Health Experiences Research Group in the lead applicant's department.

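### The planned bootstrap 95% interval for the cost-effectiveness ratio may be uninterpretable if the QALY effect is well below 0.2 SD; net monetary benefit with its interval should carry the uncertainty

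*Protocol*

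**What the plan says.** All of this is in section 10 of the protocol.

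- Economic evaluation: results will "primarily be expressed in terms of incremental cost per QALY gained between the intervention and control groups". The interval method is stated: a non-parametric bootstrap, giving 95% limits for the "mean difference of cost and QALYs between the trial groups, and incremental cost effectiveness ratios". Multiple imputation is planned for missing data. Acceptability curves will be built by the net-benefit approach.
- Economic evaluation, on costs: the protocol does not "expect the intervention to have significant impact on health and social care costs". Separately, it counts what delivery itself costs, "including development and maintenance costs for the website, advertisement costs, and the costs of monitoring participants for safety or other reasons". No amounts are given.
- Sample size: "we intend to recruit 2104 participants (i.e. 1052 per group) to this trial", giving "90% power to detect a small between group effect size of Cohen's d=0.2 at 5% two-sided significant level", after allowing for up to 50% attrition. The primary outcome is change in SPIN score. No effect on QALYs is stated.

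The protocol gives no rule for the ratio's interval when replicates fall in more than one quadrant of the cost-effectiveness plane.

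**The concern.** The sign of a cost-effectiveness ratio does not identify the result. A negative ratio means cheaper and better, or dearer and worse. A positive ratio means dearer and better, or cheaper and worse. If an appreciable share of bootstrap replicates has a QALY difference below zero, ordering the ratios mixes these cases, and the 2.5th and 97.5th percentiles no longer bound a set of plausible values. Replicates with a QALY difference close to zero also produce very large ratios of either sign.

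The trial is sized for a small effect on a symptom scale, while the denominator of the ratio is a QALY built from SF-6D, a generic utility. A smaller standardised effect on QALYs than on SPIN is plausible, although the protocol does not say so. At stake is the readability of the interval attached to the primary economic result. The estimates of cost and QALY difference are not affected.

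**Working it through.** **Step 1: the protocol's own sample size.** Inputs from the Sample size text: d=0.2, 90% power, two-sided 5%, 50% attrition. Per arm, n = 2(1.960 + 1.2816)² / 0.2² = 525.4, rounded up to 526. Then 526 / (1 − 0.5) = 1052 per arm and 2104 in total, which matches the protocol. So 526 per arm is the number with complete data if attrition reaches the planned 50%.

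**Step 2: precision of the standardised QALY difference.** SE = sqrt(2/n), which is 0.0617 SD at 526 per arm and 0.0436 SD at 1052 per arm. Because multiple imputation is planned, the effective information lies somewhere between these two.

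**Step 3: share of replicates with a negative QALY difference.** This is Φ(−d_Q / SE), a normal approximation to the bootstrap distribution. The values of d_Q are assumptions, since the protocol gives none.

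| Assumed QALY effect (SD) | 526 per arm | 1052 per arm |
|---|---|---|
| 0.03 | 31% | 25% |
| 0.05 | 21% | 13% |
| 0.10 | 5.2% | 1.1% |
| 0.15 | 0.75% | 0.03% |
| 0.20 | 0.06% | below 0.01% |

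**Step 4: quadrant shares at 526 per arm.** Further assumption: cost and QALY differences are uncorrelated. The order is dearer/better, cheaper/better, dearer/worse, cheaper/worse.

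- QALY effect 0.05 SD, no cost difference: 40 / 40 / 10 / 10%.
- QALY effect 0.05 SD, cost difference 0.1 SD: 75 / 4 / 20 / 1%.
- QALY effect 0.20 SD, no cost difference: 50 / 50 / 0.03 / 0.03%.
- QALY effect 0.20 SD, cost difference 0.1 SD: 95 / 5 / 0.06 / 0.00%.

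A positive cost difference moves replicates out of the cheaper quadrants. It leaves the negative-QALY share unchanged, because that share depends only on the denominator.

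**Step 5: the ratio limits themselves.** Percentile limits from 200,000 draws at 526 per arm with no cost difference, in units of SD of cost over SD of QALYs, compared with Fieller limits:

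- 0.05 SD: about −9.4 to 9.1; Fieller unbounded.
- 0.10 SD: about −3.5 to 3.6; Fieller unbounded.
- 0.20 SD: about −0.75 to 0.76; Fieller −0.76 to 0.76.

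At 0.05 SD, raising the cost difference to 0.1 SD widens the percentile limits to about −18 to 20.

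**Step 6: when the interval is bounded.** Fieller limits are finite only if the observed QALY difference exceeds 1.96 × SE: 0.121 SD at 526 per arm, 0.085 SD at 1052. The chance of falling short is Φ((1.96 × SE − d_Q) / SE). At 526 per arm this is 87% for a true effect of 0.05 SD, 63% for 0.10, 32% for 0.15 and 10% for 0.20. At 1052 per arm it is 79% for 0.05 and 37% for 0.10.

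**The case against.** The other side has several good points.

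- A reader might infer that the replicates are bound to cover all four quadrants. The documents do not support this. They give no QALY effect, no cost difference and no SDs. At the one effect size they do give, 0.2 SD, nearly all replicates have a positive QALY difference and the interval is usable.
- A reader might infer that the protocol expects almost no difference in total cost. Its statement covers health and social care costs only, and intervention costs are added. That expectation is also justified by mild symptoms, whereas eligibility was widened from SPIN 13–19 to 13 or more because most symptomatic people score higher.
- A reader might object that a ratio cannot come from a regression. The sentence "Regression will be used to obtain incremental cost-effectiveness ratios after controlling for baseline" is naturally read as adjusted cost and QALY differences that are then divided, so it is not a fault.
- The protocol says bootstrap without naming percentile limits, and how the limits are formed can be left to an analysis plan.
- Separate intervals for the two differences and net-benefit curves are already planned, so the decision uncertainty remains readable.

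These points make the concern conditional and minor, but they do not remove it. The protocol does commit to an interval for the ratio. No way of forming ordered limits gives a clear reading when the QALY difference is not distinguishable from zero. A larger cost difference does not help.

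**Conclusion.** The point holds in conditional form and is minor. If the QALY effect is about 0.03 to 0.10 SD with 526 per arm, roughly 31% to 5% of replicates have a negative QALY difference, they may fall in more than two quadrants, and the interval for the ratio cannot be interpreted. At 0.2 SD about 0.06% are negative and the interval works. With full information from 1052 per arm the shares fall to 25% to 1.1% over the same range of effects. The conclusion rests on assumed QALY and cost effects, zero correlation between cost and QALYs, and a normal approximation. None of these effects comes from the documents.

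**What to change.** In the Economic evaluation text of section 10, make incremental net monetary benefit (threshold × QALY difference − cost difference) with a bootstrap 95% confidence interval at stated thresholds the main summary of uncertainty. Present it alongside the intervals already planned for the cost and QALY differences, the planned acceptability curves, and a plot of the replicates on the cost-effectiveness plane. Report the ratio as a point estimate, and give it an interval only if the QALY difference is clearly away from zero.

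The cost is a change of wording. The same bootstrap replicates and net-benefit calculations are reused and no data are added. The downside is that the net-benefit interval depends on the threshold, so the thresholds should be fixed in advance.

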**11. Ethics and Governance**

We will obtain all ethics and governance permissions prior to project start and have significant experience in doing so previously. The trial protocol will be registered with ISRCTN. One of the key ethical issues for us will be to ensure we comply with the NICE guideline on social anxiety disorder, and as stated above if individuals likely to have social anxiety disorder (SPIN=19+) are identified then we will make sure they have clear advice to seek help from existing services for the NICE-recommended treatments. .We will collect data on their use of health services throughout the trial period.

We will require University ethics committee approvals from the University of Oxford and the Australian National University. We have received confirmation that we do not require NHS ethics approval (confirmed with the Health Research Agency (HRA)).

**12. Quality Assurance and Reproducibility**

The University of Oxford will take on the role of study sponsor for this study. Given the nature of this study no formal site monitoring will be conducted. Central monitoring of the progress of the study and the data quality will be provided by the Oxford Primary Care Clinical Trials Unit (PC-CTU) Quality Assurance Manager and Data Manager. An independent joint Trial Steering Committee (which in common with many ‘low risk’ trials will also have the role of Data Monitoring Committee) with independent chair and lay representation will be established to provide oversight of the conduct of the study and of the data emerging. The Committee will meet on a regular basis 6-monthly and provide advice to the Trial Management Team, which will meet monthly (with Skype to include ANU members). A representative of the Sponsor and the Funder will be invited to all Trial Steering Committee Meetings and informed of any reports to the Trial Management Team.

For reproducibility: The trial will be registered on ISRCTN prior to commencement and we will publish our final protocol (e.g. in BioMedCentral). Our Statistical Analysis Plan (SAP) will be registered and available on request. Our findings will be written up in accordance with the CONSORT statement, and in line with the Nature Publishing Group reporting checklist for Life Sciences articles, and in line with ICJME guidelines on authorship.

**13. Data Management**

Data will be collected from participants once informed consent has been received. All data will be kept confidential and held securely. The collection, transfer and storage of personal data will comply with the PC-CTU Standard Operating Procedures (SOPs), which are fully compliant with the Data Protection Act 1998 and Good Clinical Practice (GCP). Patient identifiable information (the email address and mobile telephone number used for sending reminders) will be held separate to other data during the course of the study. Otherwise, participant data will be identified only by Study ID number.

Data obtained through participant self-completion on the trial portal at baseline and all follow-up points will initially be collected and stored on ANU servers physically located in a controlled access room, with network and machine level firewalls. Once the trial is complete (last participant completed final follow-up) the trial dataset will be transferred to the Oxford clinical data management system (OpenClinica Enterprise) for analysis and subsequent archiving, using a secure encrypted (SSL) file download (access restricted by IP address). Once transferred, the database will be hosted on servers fully managed by the University of Oxford. The final anonymous trial dataset will be securely electronically archived in accordance with PC-CTU SOPs, initially for a minimum of five years. Throughout the study data monitoring and validation checks will be carried out by the Primary Care Clinical Trials Unit (PC-CTU) Quality Assurance Manager.

We will be pleased to make our final anonymous dataset available for subsequent use by others, in line with our data sharing policy, subject to ethical approval, and within the limits of participant consent. Any request for either complete or partial datasets will be considered in line with PC-CTU SOPs. The PI will consider all requests and data will be provided on the understanding that it is used for the purpose outlined in the request, that use of the dataset does not create any claim in ownership of the dataset. The PI retains ownership of the dataset and that it will not be transferred to a third party without agreement from the PI. Intellectual Property in the dataset will be jointly owned by the University of Oxford and The Australian National University, and will be detailed in a Research Collaboration Agreement between the institutions.

**14. Dissemination**

At the end of the study we will disseminate our findings widely. It is well established that getting evidence into practice is not achieved solely by producing academic outputs. To achieve effective knowledge translation we need to produce multiple outputs, in multiple formats, for multiple audiences, and we need active, ongoing engagement with stakeholders. Therefore, in addition to peer-reviewed publications (open access where possible) and conference presentations, and a full report to the funder (MQ), we will also produce three summaries of every output: for lay, policy and practitioner audiences. These will be disseminated widely as targeted hard copies to key stakeholders, include patient organisations, and available for free download from our website. Findings will also be shared on social media and through press releases (in conjunction with MQ). We will also present findings at a final workshop targeting key audiences including patients, public and their representatives.

At the end of the trial ANU are well placed to ensure the continued implementation and delivery of the self-directed version of the E-Couch social anxiety application, free of charge to the general public, should it prove effective. ANU have provided a high profile global online mental health service for 13 years.

